## Design and Methods

### Overall study design

The INFANT study is a cluster- randomised controlled trial, with first-time parent groups within local government areas, as the unit of randomization (see Figure 1). The intervention will run from three to 18 months of age (currently funded; National Health and Medical Research Council Grant No. 425801) and additional funding will be sought for follow-up to assess sustainability of outcomes. Ethical approval to conduct the study has been granted by the Deakin University Ethics Committee (ID number:EC 175-2007) and by the Victorian Office for Children (Ref : CDF/07/1138).

**Figure 1 F1:**
[figure not shown]
Study design.

### Participants and recruitment

A two-stage random sampling process will be used to select first-time parent groups. At the first stage, twelve local government areas within a 60 km radius of the research centre (Deakin University in Burwood, Victoria, Australia) will be randomly selected. Local government areas within this geographical area that have an annual birth rate lower than 600 will be excluded. At the second stage, first-time parent groups within selected local government areas will be randomly selected, proportional to the total number of first-time parent groups within each area. The first-time parents group currently underway will then be invited to participate. These first-time parent groups will be accessed initially via the MCH nurse who will set up an appropriate time to invite a member of the research team to speak with the group about the study. This team member will explain the study to the group and distribute research information packages. The packages will contain general study information, consent forms and contact details of the research team so any parent is free to contact the team to discuss any concerns or unanswered questions. A majority of group members will be required to consent to allow the group to participate in the study. Non-consenting parents within participating groups will be permitted to attend the intervention sessions, but will not be required to provide data or be contacted by the research team in any other way.

### Inclusion criteria

Parents will be eligible to participate if they are able to freely give informed consent, are first-time parents, members of a participating 'first-time parents group' and are able to communicate in English.

### Exclusion criteria

Parents will be excluded from the study if they are unable to give informed consent or are unable to communicate in English. Infants with chronic health problems that are likely to influence height, weight, levels of physical activity or eating habits will be excluded from analyses but will be permitted to participate in the study.

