### Randomization

First-time parents groups will be randomised after recruitment in order to ensure baseline equivalence and minimise selection bias. Within each local government area, first-time parents groups will be randomly allocated to the intervention or control group in order of recruitment, using a computer generated random number schedule developed by a statistician who has no contact with the centres. Prior to the first intervention session families will be informed by letter regarding the outcome of randomisation.

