### Intervention group

The intervention will be delivered by a dietitian and is comprised of six sessions delivered at three month intervals during the regular meeting time of the first-time parents' group (see Table 1). Based on an anticipatory guidance framework the intervention will incorporate a range of modes of delivery and educational strategies including brief didactic sessions, use of group discussion and peer support, exploration of perceived barriers, use of visual and written messages, follow-up delivery of messages by text-messaging and mail-outs. All educational concepts will be developed iteratively, that is, messages will be repeated and expanded upon over the course of the intervention.

**Table 1 T1:** Intervention time-frame and focus

**Infant Age**	**Emerging Behaviours**	**Anticipatory Guidance Intervention focus**
3 mo	Early weaning and introduction of solids. Introduction of nutrient poor foods. Increased muscle control, strength and coordination.	To introduce basic concepts regarding parental feeding styles and how these might relate to beliefs about parenting. To support parents to delay weaning/introduction of solids to 6 months
6 mo	Adoption by parents of a feeding style and TV viewing habits Food rejection by infants Infant starts to: sit briefly unsupported; reaches with one hand; rolls over	To develop parents understanding regarding: *feeding styles and impact on children's eating *basic nutrition principals *sedentary behaviours in families and limits to acceptability
9 mo	Increasing use of TV Parents' increased awareness of child mobility. Infant crawls and pulls self upright and walks with handhold	To develop understanding regarding: * parental modeling of eating, sedentary and physical activity behaviours * impact of eating, activity and sedentary behaviours on health of children and adults and the provision of opportunities
12 mo & 15 mo & 18 mo	Increasing autonomy of child in eating and activity Infant stands without support and beginning to walk	Continued development of themes/skills regarding: * eating and moving for health parents and children * how to feed/how to manage food rejection and demands * providing fail-safe food and activity environments

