### Control group

The control group families will receive usual care from their MCH nurse. In addition, these families will be sent general health newsletters (e.g. dental health, sun protective behaviours, general safety), and will receive Birthday and Christmas cards. These families' participation will be rewarded with gifts (to a maximum value of $15.00) on receipt of completed questionnaires.

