### Data analysis

All analyses will be conducted using the intention to treat principle. Generalized Estimating Equations (GEE) [57] will be used to fit regression models to describe the effects of the intervention on key outcome variables among parents and infants. Separate models will be fitted, to determine differences in key outcome variables in the intervention and control groups.

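### Infants with chronic health problems are randomised and then left out of the analyses, which contradicts the unqualified intention-to-treat statement; the exclusion is not limited to conditions known before allocation

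*Protocol article*

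**What the plan says.** Three sections of the protocol article bear on who is analysed.

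- **Exclusion criteria.** "Infants with chronic health problems that are likely to influence height, weight, levels of physical activity or eating habits" are the infants concerned, and they "will be excluded from analyses but will be permitted to participate in the study". The section gives no list of conditions and no date by which a condition must be known.
- **Data analysis.** "All analyses will be conducted using the intention to treat principle". No exception or modified analysis set is mentioned.
- **Randomization.** "First-time parents groups will be randomised after recruitment in order to ensure baseline equivalence and minimise selection bias". Allocation is then disclosed: "Prior to the first intervention session families will be informed by letter regarding the outcome of randomisation".

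The setting matters too. Under Overall study design, "The intervention will run from three to 18 months of age". The intervention arm receives "six sessions delivered at three month intervals during the regular meeting time of the first-time parents' group", led by a dietitian. Under Control group, "The control group families will receive usual care from their MCH nurse", with newsletters and cards in addition.

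**The concern.** Intention-to-treat means that randomised participants are analysed as allocated. A rule that enrols and randomises an infant and then removes that infant from analysis departs from this, so the article promises one analysis set and prescribes another.

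The form of the exclusion adds to the problem. It turns on whether a chronic problem is likely to affect growth, activity or eating, and the study hypotheses concern BMI gain, physical activity and diet. Nothing confines it to what was known at entry. A feeding or growth problem that becomes apparent during follow-up, when families know their arm, could fall within it. Removing infants on such information could weaken the baseline equivalence that randomising after recruitment was meant to secure. At stake are the label attached to the published analysis and, to a lesser degree, bias in the infant diet and BMI comparisons.

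**Working it through.** **1. The statements side by side.**

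| Question | Exclusion criteria | Data analysis |
|---|---|---|
| May the affected infant take part? | Yes | Not addressed |
| Is the infant allocated? | Yes, with the group, since randomisation follows recruitment | Not addressed |
| Is the infant analysed? | No | Yes, under intention-to-treat without exception |

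The last row is the contradiction. An analysis plan that followed either sentence would breach the other.

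**2. Does it affect the sample size?** The plan's figure first. Inputs from Sample size: mean 32 g, SD 15 g, 25% increase = 8 g. Two-sided 5% significance and 80% power are not stated; I assume them because they return the plan's number.

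- Per arm: 2 × (1.960 + 0.842)² × 15² / 8² = 55.2, rounded up to 56; total 112, as stated.
- Design effect: 1 + (10 − 1) × 0.2 = 2.8; 112 × 2.8 = 313.6.
- Attrition 40%: 313.6 / 0.6 = 522.7.
- Oversampling 15%: 522.7 × 1.15 = 601.1, consistent with 600.

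Now remove an assumed fraction x of infants from analysis. Effective number per arm = 600 × 0.6 × (1 − x) / 2.8 / 2.

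| x (assumed) | Effective n per arm | Power |
|---|---|---|
| 0 | 64.29 | 85.6% |
| 2% | 63.00 | 84.9% |
| 5% | 61.07 | 83.8% |
| 10% | 57.86 | 81.8% |

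Power stays above 80% throughout, so power is not the issue.

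**3. How large could a bias be?** The document gives neither an exclusion rate nor the outcome level of excluded infants, so every input here is an assumption. Suppose excluded infants lie s SD from their arm's mean, all in the same direction, with fractions e1 and e0 excluded in the two arms. The spurious shift in the arm difference is, in absolute size,

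s × [e1/(1 − e1) − e0/(1 − e0)].

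- s = 1, 5% v 2%: 0.0526 − 0.0204 = 0.032 SD.
- s = 1.5, 5% v 2%: 1.5 × 0.0322 = 0.048 SD.
- s = 1.5, 8% v 3%: 1.5 × (0.0870 − 0.0309) = 0.084 SD.
- Equal fractions in both arms with the same s: zero.

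**4. Against what scale?** The planned effect is 8/15 = 0.53 SD, so these shifts are 6% to 16% of it. With 180 infants per arm after attrition and design effect 2.8, the standard error of the difference is √(2 × 2.8/180) = 0.18 SD, and the largest shift is just under half of that. If attrition instead thinned groups from ten to six, the design effect would be 1 + 5 × 0.2 = 2.0, the standard error √(2 × 2.0/180) = 0.15 SD, and the largest shift a little over half.

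**The case against.** A reader might infer that the plan sets up an arm-dependent exclusion after randomisation. The document does not say that, and there are good grounds for a milder reading.

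- The rule sits among the entry criteria. It reads naturally as a way of not turning an infant away from an existing social group, much as non-consenting parents may attend sessions without giving data. Recruitment precedes allocation, so many such conditions could be known beforehand. Excluding on a pre-randomisation characteristic, judged blind, does not bias the comparison and is commonly accepted as modified intention-to-treat.
- Differential detection is not established. Table 2 schedules infant anthropometry at all six ages without distinction by arm, control families keep their nurse, and the Background cites about 35 health-care visits in the first year. The dietitian is given an educational role, not a diagnostic one, and nobody unblinded is named as applying the exclusion.
- Only infants are named. The document does not say that parents' own outcomes are dropped, so a claim that every analysis loses these families goes too far.
- Who judges the condition, and when, are details that a condensed article may leave to the full protocol or analysis plan.

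Most of this stands, and it limits the point. It does not remove the conflict: the article itself fixes both the exclusion and an unqualified intention-to-treat claim. The benign reading needs a limit to baseline conditions that the text does not state.

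**Conclusion.** The contradiction between Exclusion criteria and Data analysis is certain on the text. The risk of arm- or outcome-dependent exclusion is something the wording allows, not something it prescribes. Its size cannot be derived from the document. The 0.03 to 0.08 SD range rests wholly on assumed rates, assumed distances and a common direction of deviation, although chronic problems could push growth or intake either way. Even so it is modest beside both the planned effect and the sampling error. The 600 target is unaffected. This is a should-fix: the bias is probably small, but the analysis set is defined in two incompatible ways, and it should be settled before outcome data are seen.

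**What to change.** Choose one of two wordings and make Exclusion criteria and Data analysis agree.

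1. **All infants in the primary analysis.** Analyse every randomised consenting infant with outcome data, and use the chronic-illness exclusion as a sensitivity analysis. Cost: a few atypical infants add slightly to outcome variance, and one further analysis is run.
2. **A baseline-limited set.** Restrict the exclusion to conditions documented at or before the baseline assessment, judged by someone blind to arm and outcome. Call the set modified intention-to-treat in Data analysis, and report the number excluded and the reasons by arm. Cost: the primary set loses the plain intention-to-treat label.

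Under either option, add a clause saying whether the parents of such infants still contribute to the parent outcomes. The whole change is a few sentences of wording and needs no change to recruitment or sample size.

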### Sample size

A sample of 600 first time parents participating in first-time parents' groups (300 in each arm) will be recruited for the study. The sample size calculation is based on detecting changes in one of the main outcomes: dietary intake. The authors are not aware of any data providing means and standard deviations on physical activity, sedentary behaviours or body mass index in this age group. Consequently, sample size calculations were undertaken for dietary outcomes using three day weighed food data on 18 month old Australian children [13,48].

As there are no quantitative dietary recommendations for children less than four years old in Australia, we suggest a 25% increase in vegetable consumption as a minimum target on which the sample size calculations are based. Australian data show that 18-month old children eat around 32 grams of vegetables (not including potato) per day with a standard deviation of 15 g [48]. To detect an increase in vegetable consumption as small as 25% the total number of subjects required is 112 (56 in each arm). To account for within-group clustering (resulting from randomisation at the first- time parent group level) the sample size was increased by the design effect/inflation factor of 2.8, based on assumptions of each cluster consisting of approximately ten people and a conservative inter-class cluster coefficient of 0.2. The sample size estimation was further adjusted to account for attrition (40%) with the potential of loss of entire groups to follow-up and we plan to over sample by 15%. Thus the final sample is 600 (300 in each arm).

### Randomization

First-time parents groups will be randomised after recruitment in order to ensure baseline equivalence and minimise selection bias. Within each local government area, first-time parents groups will be randomly allocated to the intervention or control group in order of recruitment, using a computer generated random number schedule developed by a statistician who has no contact with the centres. Prior to the first intervention session families will be informed by letter regarding the outcome of randomisation.

### Intervention group

The intervention will be delivered by a dietitian and is comprised of six sessions delivered at three month intervals during the regular meeting time of the first-time parents' group (see Table 1). Based on an anticipatory guidance framework the intervention will incorporate a range of modes of delivery and educational strategies including brief didactic sessions, use of group discussion and peer support, exploration of perceived barriers, use of visual and written messages, follow-up delivery of messages by text-messaging and mail-outs. All educational concepts will be developed iteratively, that is, messages will be repeated and expanded upon over the course of the intervention.

**Table 1 T1:** Intervention time-frame and focus

**Infant Age**	**Emerging Behaviours**	**Anticipatory Guidance Intervention focus**
3 mo	Early weaning and introduction of solids. Introduction of nutrient poor foods. Increased muscle control, strength and coordination.	To introduce basic concepts regarding parental feeding styles and how these might relate to beliefs about parenting. To support parents to delay weaning/introduction of solids to 6 months
6 mo	Adoption by parents of a feeding style and TV viewing habits Food rejection by infants Infant starts to: sit briefly unsupported; reaches with one hand; rolls over	To develop parents understanding regarding: *feeding styles and impact on children's eating *basic nutrition principals *sedentary behaviours in families and limits to acceptability
9 mo	Increasing use of TV Parents' increased awareness of child mobility. Infant crawls and pulls self upright and walks with handhold	To develop understanding regarding: * parental modeling of eating, sedentary and physical activity behaviours * impact of eating, activity and sedentary behaviours on health of children and adults and the provision of opportunities
12 mo & 15 mo & 18 mo	Increasing autonomy of child in eating and activity Infant stands without support and beginning to walk	Continued development of themes/skills regarding: * eating and moving for health parents and children * how to feed/how to manage food rejection and demands * providing fail-safe food and activity environments

### Control group

The control group families will receive usual care from their MCH nurse. In addition, these families will be sent general health newsletters (e.g. dental health, sun protective behaviours, general safety), and will receive Birthday and Christmas cards. These families' participation will be rewarded with gifts (to a maximum value of $15.00) on receipt of completed questionnaires.

### Measures

Parent and infant data will be collected using parent self-completion questionnaires, apart from infant dietary intake data which will be collected by telephone interview. As outlined in Table 2, all data (appropriate to the age of the child) will be collected every three months, corresponding with the six intervention sessions. Repeated data collection is necessary given the rapid changes in height, weight, eating and activity behaviours in infants. The measures collected are detailed below.

**Table 2 T2:** Measures and time-frame for the study

Intervention timeline – year		1		2			3
Measures		Infant Age					
		3 months	6 months	9 months	12 months	15 months	18 months

Dietary Intake	Parent	✓					✓
	Child	✓	✓	✓			✓
Sedentary behaviour	Parent	✓					✓
	Child			✓			✓
Physical activity	Parent	✓					✓
	Child		✓	✓	✓	✓	✓
Family Food Environment	Parent	✓		✓			✓
Family physical activity & Sedentary Environment	Parent	✓		✓			✓
Demographic Data	Parent	✓					
Anthropometric Data	Parent	✓					✓
	Child	✓	✓	✓	✓	✓	✓

#### Dietary intake

Dietary intake for mother and father will be assessed using The Cancer Council's Dietary Questionnaire for Epidemiological Studies (Version 3) at baseline and study conclusion. This questionnaire is an updated version of the semi-quantitative food frequency questionnaire specifically developed for the Melbourne Collaborative Cohort Study [49]. Child's dietary intake will be assessed by telephone-administered multi-pass 24-hour recall with parents [50]. Visual aids will be provided to primary carers in advance of interviews to help in the estimation of quantities of food consumed. Three days of dietary data will be collected (including one weekend day) when the infant is 9 and 18 months of age.

#### Physical activity

Parents will report their frequency and duration in physical activity during the previous week using the Active Australia Survey [51]. In addition, at 12 and 18 months parents will be asked to report the number of hours their child typically spends playing outdoors on weekdays and weekend days.

#### Sedentary behaviors

Parents will be asked the amount of time the infant spends watching television on a typical weekday and on a typical weekend day [52], and to estimate the amount of time each day that the child spends immobile. Parents will also report the total time they spend watching television during their leisure-time in a typical week [53].

#### Home food environment

Three aspects of the home food environment will be assessed. Aspects of nutrition knowledge focused around nutrition targets of the intervention will be assessed modified subscales of the validated Nutrition Knowledge Questionnaire [54], Parent Feeding Style will be assess using the Child Feeding Questionnaire (CFQ) [55], the Caregivers Feeding Style Questionnaire CFSQ [56].

#### Family physical activity and sedentary environment

Parents will be asked general questions relating to their knowledge about physical activity in early childhood, their interactions with their child around physical activity and an audit checklist on the physical activity and sedentary home environment.

Standard demographic and socio-economic information will be collected by parental report. Anthropometric measures (height/length and weight) on the infant and parents will be collected by trained staff.

### Data analysis

All analyses will be conducted using the intention to treat principle. Generalized Estimating Equations (GEE) [57] will be used to fit regression models to describe the effects of the intervention on key outcome variables among parents and infants. Separate models will be fitted, to determine differences in key outcome variables in the intervention and control groups.

## Discussion

The prevalence of obesity in early childhood is rapidly increasing and is determined, in part, by eating, physical activity and sedentary behaviours. These behaviors are predominantly learnt at home in the first five years of life, and impact upon health throughout life. Given this, the early years hold promise as a time when obesity prevention may be most effective. However, research in this early period of life is lacking. This cluster-randomized trial will be one of the first to investigate whether a health promotion program delivered to first-time parents in their usual social settings can promote healthy eating, physical activity and reduced sedentary behaviours in infants. If effective, this program could protect children from the development of obesity and its associated social and economic costs. Further this study has the capacity to substantially strengthen our understanding of strategies that will promote health among families and may result in policy change both nationally and internationally.
